#### Feasibility of recruitment

Given the planned inclusion period of 12 months and the 18 centers participating and with an expected 100 inclusions a year (~ 2 per week), accounting for patients who are not willing to participate, we expect to have sufficient numbers for our hypothesis. The length of the inclusion period is based on the inclusion rate of the assumed slowest including hospitals (UMCs).

#### Data management

All data are handled confidentially and anonymized in compliance with the Dutch Personal Data Protection Act (“Wet Bescherming Persoonsgegevens”). Questionnaires are collected digitally, and the patient study data are stored in a coded way using secured data management software system Castor EDC [44]. In case an email address is not available, a paper case report form is sent to the patient. When patients fill in their questionnaires on paper, documentation is stored in the investigator site file. Each patient is assigned a random study number that is used for all documentation, study reports and publications. The key to this study number is handled by an independent researcher. All data will be stored during the study period in Castor EDC, after the study is finished the data will be stored for 15 years. Documentation, such as questionnaires filled in on paper and signed informed consent forms, stored in the investigator site file will be stored at each site.

## Statistical analysis

The results will be analyzed separately for TKA and THA. We will analyze patients as treated.

### Primary outcome measure

The difference between both groups in change of KOOS-PS/HOOS-PS between baseline and 3 months follow-up score will be used as primary outcome. Patients will be analyzed as treated.

The primary analyses will be performed by using mixed models (change in KOOS-PS/HOOS-PS during 3 months as dependent and intervention as independent variable). Change between baseline and 3 months follow-up score will be used as primary outcome. Hospital variable will be used to indicate the correlation structure in the model. Adjustments will take place for baseline values of KOOS-PS/HOOS-PS. Of variables of which a priori is known that they are associated with the change in KOOS/HOOS-PS, based on previous studies or based on a strong clinical rationale will be considered as covariates in the primary analysis. These covariates are age, gender, BMI, and surgical approach in THA (anterior, lateral and postero-lateral). The assumptions of constant variance and linear relationships will be assessed. Should any of these assumptions seriously fail then transformation of the dependent or independent variable(s) (where applicable) will be used. The choice of which transformation (e.g. square root, logarithm) will be used will be based on the specific distribution of the residuals.

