### Assessments

Patients will be asked to fill in questionnaires at baseline, and at 6 weeks, 3- (primary end-point), 6-, 9 and 12-months follow-up. Performance-based tests will be performed at baseline, 6- and 12 months (see Table 1 for an overview). In each participating hospitals an assessor will be trained by the coordinating researcher to perform these Performance-based tests.

**Table 1 Tab1:** Overview of measurement PATIO study

Timepoint	Allocation	Enrolment	Post-allocation	Close-out
	Randomization	Baseline, at inclusion	6 weeks,3, 6, 9 –months follow-up	12-months follow-up
Enrolment				
Eligibility screen		X		
Informed consent		X		
Allocation	X			
Interventions				
*Intervention group: Treat to target*			X	X
*Control group:* *Usual care*			X	X
ASSESSMENTS:				
*Demographic;* age, gender, side affected, BMI, education level, comorbidity		X		
*HOOS-PS / KOOS - PS*		X	X	X
*OHS / OKS*		X	X	X
*NRS*		X	X	X
*AAQ*		X	X (only at 3 months)	X
*EQ 5-D5L*		X	X	X
*Satisfaction question*			X	X
Cost-effectiveness			X	X
*Performance-based tests*		X	X (only at 3 months)	X
*(Serious) Adverse events*			X	X

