### Primary outcome

We propose a cluster RCT (randomization on hospital level) with an intracluster correlation coefficient of 0.06 and in total 18 participating hospitals. Sample sizes of 90 in group one and 90 in group two, which were obtained by sampling 9 clusters with an average of 10 subjects each in group one (180 patients) and 9 clusters with an average of 10 subjects each in group two (180 patients), achieve 90% power to detect a difference between the group means of at least 10. The coefficient of variation of cluster sizes is 0,500. A two-sided t-test was used with a significance level of 0,05. This test used degrees of freedom based on the number of subjects. To account for a 25% of drop out 240 TKA and 240 THA patients will be needed.

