### Secondary outcomes

By using repeated measures mixed models analyses the course of the secondary outcome(s) over time of both interventions will be compared. The following time points will be used, baseline and follow-up measurements at 6 weeks, 3, 6, 9, 12 months.

Change in secondary outcomes will be used as dependent variable. As secondary outcomes will be used: KOOS-PS/HOOS-PS; OKS/OHS, NRS, AAQ, EuroQol-5D-5L, performance-based test and the anchor and satisfaction questions.

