#### Economic evaluation

The economic evaluation will consist of a cost-utility analysis from a societal perspective (costs per QALY), based on patient reports and with an undiscounted one-year time horizon. Average costs and outcomes will be statistically compared using net-benefit analysis, with multiple imputation to account for missing data. Quality-adjusted life years (QALYs) will be estimated using the Dutch tariff for the quarterly EQ-5D-5L measurements. Societal costs will include healthcare costs, patient and family costs, and productivity costs. The timing, contents, frequency and duration of PPT will be measured using the study registrations. Other healthcare use and productivity will be reported by patients using quarterly questionnaires (including general practitioner visits, outpatient visits, hospital days, medication, home and informal care, patient costs, absence from work, and productivity while at (unpaid) work). Healthcare will be valued using reference prices obtained from the Dutch guidelines for economic evaluations in healthcare, including time and travel costs. Sensitivity analysis will be performed on the cost perspective (healthcare instead of societal perspective), the valuation of productivity (human capital instead of friction cost approach) and the utility measure used to calculate QALYs (Visual analogue scale for health (with power transformation) instead of Dutch EQ-5D-5L tariff).

In addition to the CUA, a budget impact analysis (BIA) will be performed. In a cost-calculator spreadsheet model, budget impact will be evaluated from the perspectives of the Dutch ‘Budgettair Kader Zorg’ (BKZ), health insurers, and the different care providers. The analysis will take into account the current mix of treatments, with prices appropriate for the perspective, a 4-year time-horizon and different scenarios for the rate of uptake.

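### The primary model as written cannot use the 6-week scores of patients who lack a 3-month score, and so is open to avoidable bias if loss differs by arm

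*Protocol article*

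**What the plan says.** All places are in the protocol article.

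- **Statistical analysis, Primary outcome measure.** The mixed model is specified as "change in KOOS-PS/HOOS-PS during 3 months as dependent and intervention as independent variable". The dependent variable is a single change score: "Change between baseline and 3 months follow-up score will be used as primary outcome". The only dependence between observations that is named is between patients of the same hospital: "Hospital variable will be used to indicate the correlation structure in the model". The model adjusts for baseline score, age, gender, BMI and, for hips, surgical approach.
- **Assessments and Table 1.** The function score is collected before the primary time point as well: "Patients will be asked to fill in questionnaires at baseline, and at 6 weeks, 3- (primary end-point), 6-, 9 and 12-months follow-up".
- **Statistical analysis, Secondary outcomes.** The 6-week scores are used here: "By using repeated measures mixed models analyses the course of the secondary outcome(s) over time of both interventions will be compared". KOOS-PS/HOOS-PS is on the list of these outcomes, and the visits are given as: "The following time points will be used, baseline and follow-up measurements at 6 weeks, 3, 6, 9, 12 months".
- **Economic evaluation.** This is the one analysis with a named method for incomplete data: "with multiple imputation to account for missing data".
- **Sample size.** Loss is allowed for: "To account for a 25% of drop out 240 TKA and 240 THA patients will be needed". The secondary pain outcome raises the target to 312 per joint, with the same 25% allowance. Neither statement says at what time the 25% applies.

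**The concern.** A model with one baseline-to-3-month change per patient needs both scores. A hospital random effect does not bring back a patient whose 3-month score is missing, and a 6-week score has no place in the model. Unless something is added, the primary estimate is an observed-case estimate.

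Baseline adjustment protects against loss that depends on baseline function. It does not protect against loss that depends on recovery in the first weeks, if that dependence differs between arms. Such a difference is conceivable. The trial is open-label. Intervention patients see trained therapists who check them regularly against milestones, whereas the use of therapy in the control arm is discretionary. The 6-week score is the measurement that would carry this information, and it is already being collected.

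**Working it through.** **1. The plan's own figures.** Inputs from the sample size section: difference 10, SD 15.6, ICC 0.06, 9 hospitals per arm, 10 patients per hospital, coefficient of variation of cluster size 0.5, two-sided 5%, degrees of freedom from subjects.

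- Design effect = 1 + ((0.5² + 1) × 10 − 1) × 0.06 = 1.69.
- SE = 15.6 × √(2 × 1.69 / 90) = 3.02, and 10 / 3.02 = 3.31.
- Power is 0.908 by the noncentral t with 178 degrees of freedom, against 90% stated.
- Enrolment: 180 / 0.75 = 240 and 234 / 0.75 = 312. Both reproduce.

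**2. Is power threatened?** At 312 per joint and 25% loss, 234 remain, or 13 per hospital.

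- Design effect = 1 + (1.25 × 13 − 1) × 0.06 = 1.915.
- SE = 15.6 × √(2 × 1.915 / 117) = 2.82.
- Power is about 94%, and still about 91% with 16 hospital-based degrees of freedom.

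So power is not the issue.

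**3. How many patients are affected?** At most 312 − 234 = 78 per joint, if the whole 25% were lost by 3 months. At 10% the number is about 31.

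**4. Size of the bias.** The documents give no correlations and no pattern of loss, so these are assumptions: 0.4 for baseline with each later score, 0.7 for 6 weeks with 3 months, SD 15.6, true difference 10. Loss follows a logistic model in the 6-week score.

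Suppose the patients who remain in one arm have a 6-week mean shifted by δ SDs. The baseline-adjusted bias is then roughly

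(0.7 − 0.4 × 0.4) × 15.6 × δ = 8.4 δ points.

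For weak dependence, δ is about ln(odds ratio per SD) × proportion lost. With an odds ratio of 1.65 (log 0.5), this gives 8.4 × 0.5 × 0.25 = 1.05 points at 25% loss and 8.4 × 0.5 × 0.10 = 0.42 at 10%. The shortcut overstates strong dependence, so the table comes from large-sample simulation.

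| Dependence of loss on worse 6-week function | 10% lost in each arm | 25% lost in each arm |
|---|---|---|
| None | 0 | 0 |
| Equal in both arms | 0 | 0 |
| One arm only, odds × 1.65 per SD | 0.4 | 1.0 |
| One arm only, odds × 4.5 per SD | 1.1 | 2.4 |

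The effect is understated if the control arm loses its poorer patients, and overstated if the intervention arm does.

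**5. Sensitivity to the assumptions.**

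- With the 6-week to 3-month correlation varied from 0.5 to 0.8, a baseline to 3-month correlation of 0.35, 25% loss and one-arm dependence at odds × 1.65, the estimate is 9.29 down to 8.72. The bias is therefore 0.7 to 1.3 points.
- Equal dependence in both arms but unequal loss (30% against 20%) gives a bias of about 0.5 points.

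**6. What the 6-week score recovers.** If every patient lost by 3 months gave a 6-week score, an estimator that uses it returns about 10.0 in all these scenarios. If 60% gave one, about 55 to 70% of the bias goes, and up to about 0.75 points remain. With random loss the gain in precision is small: SE 2.46 against 2.40.

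**The case against.** **The article is condensed.** It nowhere says that patients without a 3-month score are excluded, and an unseen SAP may add imputation. This stands in part. The article's silence on missing primary data is no finding, and observed-case is an inference. But the article does fix the primary model, and that model cannot take in a 6-week score unless something is added to it.

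**The secondary model is not simply better.** A reader might infer that the authors chose the weaker of two models they describe. The text does not support this. The secondary repeated-measures description names no hospital effect, baseline adjustment or covariates, and the primary model has all three. What is recommended below combines the two.

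**The 6-week scores are not ignored.** True. The secondary analysis of the same scale uses them and is a partial check, but it does not supply the primary estimate.

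**The 25% is not a 3-month figure.** True. A reader might infer that a quarter of primary outcomes will be missing. The allowance belongs to a 12-month study and its timing is not given, which is why 10% is shown beside it.

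**The mechanism is speculative.** Questionnaires are collected digitally or on paper, not by the treating therapist, and control patients also get a physiotherapy referral as standard at discharge. An open-label design does not by itself produce loss that depends on recovery in one arm only. This stands: the bias is a possibility, not a prediction. The upper end of the range needs the odds of loss to rise about 4.5-fold per SD in one arm and stay flat in the other.

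**Conclusion.** The point holds as a cheap improvement to the primary analysis. As written, the model leaves out patients without a 3-month score and cannot use their 6-week scores. Under the assumed correlations and one-arm dependence, the resulting bias is about 0.4 to 1.1 points at 10% loss and 1.0 to 2.4 points at 25% loss, on a 10-point effect and of either sign. It is zero if loss is random, or depends on 6-week function equally in both arms at equal rates.

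The documents do not support saying that the primary result will be biased, that the effect will be understated, or that the trial loses power. The first two depend on a pattern of loss the documents do not describe, and the power check contradicts the third.

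**What to change.** Take the primary 3-month arm difference from a repeated-measures mixed model of the 6-week and 3-month scores. Include arm-by-time terms, a hospital random effect, unstructured within-patient covariance, the baseline score and the covariates already listed for the primary analysis. Include every patient with at least one of the two follow-up scores.

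Alternatively, keep the stated primary model and extend to it the multiple imputation planned for the economic evaluation, with arm, hospital, baseline score and 6-week score in the imputation model.

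In either case, keep the observed-case version of the stated model as a sensitivity analysis. Inclusion was still under way when the article was written. Provided the change is made before the outcome data are analysed, it can be prespecified.

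The cost is a few lines of text and slightly more modelling, with no new data. The estimate then relies on data being missing at random given the 6-week score. Patients who lack both follow-up scores are not recovered.

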### Primary outcomes

#### Physical functioning

Physical functioning, assessed by the 5-item short version of the validated Dutch translation of the Hip disability and Osteoarthritis Outcome Score (HOOS) [24, 25] or the 7-item short version of the Dutch translation of the knee injury and Osteoarthritis Outcome Score (KOOS) questionnaire [26, 27]. Function scores will be determined on a scale from 0 (severe impairments in function) to 100 (no impairments in function).

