## Sample size and power calculation

Our primary research hypothesis is that the improvement in physical function in our “treat-to-target” intervention will be superior to the improvement in the usual care group at 3 months, measured by the HOOS-PS/KOOS-PS score.

The power calculation is based on the proof of superiority, and calculated for patients undergoing TKA and THA separately. The reported standard deviation (SD) of the KOOS-PS and HOOS-PS 3 months after physiotherapy in TKA and THA patients was 15.6 and 11.8, respectively [35–41]. For the intra cluster correlation coefficient we used an interclass correlation coefficient (ICC) of 0.06, which is generally reported in literature for hospital processes. To detect superiority of the treat-to-target PPT intervention to usual PPT we assessed the required sample size based on the following assumptions, a minimally clinical important difference (MCID) of 10 points, and a SD of 15.6. Since a MCID of the KOOS-PS and HOOS-PS after postoperative physiotherapy in TKA/THA patients is not yet available, a MCID was chosen based on expert opinion, namely 10 points on the KOOS-PS and HOOS-PS [42, 43].

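### The primary change score may be transformed according to its residuals, but the example functions do not suit negative changes and the effect would leave the points scale of the 10-point MCID

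*Protocol article*

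**What the plan says.** Under Statistical analysis, Primary outcome measure, the protocol article fixes the endpoint: "Change between baseline and 3 months follow-up score will be used as primary outcome". The model is a mixed model with intervention as the independent variable, hospital defining the correlation structure, and adjustment for the baseline score, age, gender, BMI and, in THA, surgical approach. TKA and THA are analysed separately.

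Model checking follows: "The assumptions of constant variance and linear relationships will be assessed". The remedy is: "Should any of these assumptions seriously fail then transformation of the dependent or independent variable(s) (where applicable) will be used". The choice of function is also stated: "The choice of which transformation (e.g. square root, logarithm) will be used will be based on the specific distribution of the residuals".

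Two other sections bear on this. Physical functioning gives the scale: "Function scores will be determined on a scale from 0 (severe impairments in function) to 100 (no impairments in function". Sample size and power calculation plans in raw points: "a minimally clinical important difference (MCID) of 10 points, and a SD of 15.6".

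**The concern.** The remedy is a stated rule for the primary analysis, and it names the dependent variable as a candidate for transformation. That raises two difficulties for this endpoint.

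- **Domain.** The dependent variable is a signed difference. The two example functions are made for non-negative or positive quantities, so they cannot be applied to patients who got worse (or, for the logarithm, to those with no change) without a constant being added. The size of that constant affects the result, and it would be settled after the data are seen.
- **Scale.** The trial is planned to detect a difference in mean change in points. After a non-linear transformation the model estimates something else, and a 10-point difference no longer has one value on the new scale.

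At stake is whether the primary result can be read against the difference the trial was sized for, and whether the primary scale is fixed before the data are known. Because the joints are analysed separately, the rule could also leave knee and hip on different scales.

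**Working it through.** **1. The plan's own figure, on the raw scale.** Inputs from Sample size and power calculation: difference 10, SD 15.6, "an intracluster correlation coefficient of 0.06 and in total 18 participating hospitals", 9 hospitals per arm with 10 patients each per joint, coefficient of variation of cluster size 0.5, two-sided alpha 0.05.

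- Design effect = 1 + ((1 + 0.5²) × 10 − 1) × 0.06 = 1.69
- SE = 15.6 × √(2 × 1.69 / 90) = 3.02
- 10 / 3.02 = 3.31, and 3.31 − 1.96 = 1.35, giving power of about 91% (90.8% by noncentral t with 178 df)
- Dropout: 180 / 0.75 = 240 per joint

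The stated 90% and 240 are reproduced. They belong to a difference in means measured in points.

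**2. Range of the dependent variable.** Each score runs from 0 to 100, so change can run from −100 to +100. The logarithm requires change > 0, the square root change ≥ 0. The square root of zero is defined, so zero change is a problem for the logarithm only.

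**3. What 10 points becomes after transformation.** The offsets are assumed, since the article states none.

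| Step in change | √x | √(x + 100) | log(x + 101) |
|---|---|---|---|
| 0 to 10 | 3.16 | 0.488 | 0.094 |
| 20 to 30 | 1.00 | 0.447 | 0.079 |
| 40 to 50 | 0.75 | 0.415 | 0.069 |

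The same 10 points takes a different value at each level. An offset removes the domain problem and softens the curvature, but the effect is still not in points.

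**4. How many patients could be affected (illustration only).** The article gives neither a mean nor an SD of change. The SDs it quotes describe scores "3 months after physiotherapy in TKA and THA patients was 15.6 and 11.8, respectively", that is, at follow-up. With baseline SD s₀, follow-up SD s₃ and correlation ρ:

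SD of change = √(s₀² + s₃² − 2ρ·s₀·s₃)

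If s₀ = s₃, this equals s₃ when ρ = 0.5, is smaller for higher ρ and larger for lower ρ. The follow-up SDs are therefore a stand-in, with 20 added as a wider case. With normal change, P(change ≤ 0) = Φ(−mean / SD):

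| Assumed mean improvement | SD 11.8 | SD 15.6 | SD 20 |
|---|---|---|---|
| 10 | 19.8% | 26.1% | 30.9% |
| 15 | 10.2% | 16.8% | 22.7% |
| 20 | 4.5% | 10.0% | 15.9% |
| 25 | 1.7% | 5.5% | 10.6% |
| 30 | 0.6% | 2.7% | 6.7% |

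At means of 15–20 with the quoted SDs the share is 4.5–16.8%. That is 180 × 0.045 = 8 to 180 × 0.168 = 30 of the 180 analysed patients per joint in the primary calculation, or about 11 to 39 of the 234 implied by the larger NRS-based target. These counts matter only if the outcome itself is transformed by one of the example functions without an offset.

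**The case against.** The other side has a good deal to say.

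- **The rule is conditional and open.** It applies only on serious failure of an assumption, it covers dependent or independent variables where applicable, and the two functions are examples. A reader might infer that the change score is to be log or square-root transformed; the article does not say so. The natural answer to non-linearity is to transform age, BMI or the baseline score, which leaves the outcome in points. This stands and limits the point to the dependent-variable branch.
- **Nobody is said to be dropped.** A reader might infer that patients who fail to improve would be lost, biasing the comparison. The article states no such exclusion. An analyst who met an undefined value would more likely add an offset or try another function. This stands.
- **The choice is not said to be unblinded.** The trial is open-label, but the article does not say who inspects the residuals or whether the arms are masked, and it says trial management stayed blind to the randomization. What the text supports is that the choice depends on the data.
- **The size rests on assumed means and a substituted SD.** This stands, so the figures are illustrative.
- **Offsets and back-transformation belong in an SAP.** Agreed, and their absence is not the point.

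What survives is what the article itself states: the dependent variable is expressly included, and the examples offered do not fit a signed variable. The qualifier about applicability could be read as excluding unsuitable functions, but it does not keep the outcome in points.

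**Conclusion.** The concern holds in a limited form. The article permits the signed primary change score to be transformed, by a function chosen from the trial's residuals, if constant variance or linearity seriously fails. Its example functions do not suit that variable without an arbitrary constant fixed after the fact. Any non-linear transformation of the outcome would also separate the primary effect from the 10-point MCID and from the power calculation.

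The scale mismatch follows from the article's own text and needs no numerical assumption. The share of patients with change of zero or below, about 4.5–17%, does: it assumes normal change, follow-up SDs standing in for the SD of change, and a mean improvement of 15–20 points. Across the wider grid it runs from under 1% to about 31%. Whether the problem arises at all depends on the residuals and on which variable is transformed. The stated power and sample size are not in question.

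**What to change.** Replace the two sentences on transformation in Primary outcome measure with a rule along these lines:

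> The primary effect is the baseline-adjusted difference in mean change, in raw KOOS-PS/HOOS-PS points, and remains so whatever the residuals show. If variance appears unequal, cluster-robust intervals with a small-sample correction, or intervals from a bootstrap by hospital, are reported as a sensitivity analysis. If the relation with a continuous covariate is not linear, a pre-stated flexible term (such as a spline) is used for that covariate. A transformed outcome may be reported only as a sensitivity analysis.

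The small-sample correction matters because there are only 9 hospitals per arm. Any SAP should carry the same rule for both joints.

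Cost: two sentences of text and slightly more analysis work. No new data are needed and no sample-size figure changes. The one real downside is some possible loss of efficiency if residual variance turns out to be strongly non-constant.
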